The addition of primary contact physiotherapists in the ED is an emerging model of care that aims to optimize patient flow while in the ED [25]. Several studies conducted in recent years have shown that this model of care is associated with reduced time waited before receiving care, and reduced length of stay in the ED, as well as fewer unnecessary consultations with various health professionals, and less prescriptions of imaging tests and medication, including opioids, and over-the-counter medication [8, 26–29]. In addition, this model of care was associated with fewer repeat visits to the ED for a similar condition for up to one month after the initial ED visit [29]. Thus, management by a primary contact physiotherapist appears to be associated with decreased service and resource use, both at the ED and up to several weeks later. However, very few studies having investigated primary contact physiotherapist care in the ED have looked at its cost-effectiveness.

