## Materials and methods

### Study design and costing approaches

This study is composed of three distinct designs, one per objective. The costing approach used for Objective 1 will be Time-Driven Activity-Based Costing (TDABC), which involves determining the per-minute costs associated with each care process included in a care pathway by multiplying the cost per minute of each care process by its duration. Details on this costing approach and its application to the ED have been described by one of the authors elsewhere [36]. Objective 2 will be achieved through a cost-utility analysis approach in which health care costs at the ED visit and those reported at the 1- and 3-month follow-ups will be compiled and combined with the utility scores obtained at the same measurement times, from both Health system and Societal perspectives. Cost-utility analysis is favored in Canada since it uses a generic outcome measure allowing comparison of the health gains associated with several different interventions, such as different models of care [35].

The ICER between the three ED models of care for the management of MSKDs over a two-year period (Objective 3) will be estimated using a cost-effectiveness analysis via a hybrid mathematical model. This model will consist of a decision tree covering the period from the initial ED visit up to three months post-initial visit, and a Markov model starting three months post-initial ED visit and ending 24 months (two years) after the ED visit. The decision tree provides a simple and clear illustration of a patient’s possible short-term care pathways following a new intervention [35, 37]. In addition to reporting the different interventions used, the decision tree also allows for the inclusion of adverse events following the initial intervention, such as a new ED visit for the same condition, and for repeating an intervention over time as needed (e.g., new visit in the ED a few days after the initial visit and then a new visit two months later for the same condition) [35, 37]. It also permits to determine the proportion of disability associated with each of the three ED models of care.

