### Study outcomes

Primary outcomes used to measure the average cost of an ED visit (Objective 1) will be the costs of care processes and the time associated with each care process. This method of costing is routinely used by some members of the research team [36, 45, 46]. The costs related to ED management (medical and non-medical staff, imaging, medication, consumables, maintenance, etc.) were obtained via a formal request made by a member of the research team to the CHU de Québec–UL Finance Department. The time associated with each care process was calculated by a member of the research team using estimates provided by the CHUL medical and non-medical staff that were validated during an observation period in the ED [36, 45]. Uncertainty in measured times will allow the variability of ED costs to be considered, and to derive a distribution of possible costs at baseline for each participant.

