As part of the cost-utility analysis (Objective 2) and hybrid mathematical model (Objective 3), the efficiency of the ED models of care will be assessed using an incremental cost-effectiveness ratio (ICER). The resulting ICER will be reported in terms of incremental cost per quality-adjusted life years (QALY) gained, between the models of care. The follow-up costs of each participant recorded via the self-administered follow-up questionnaires completed at 1 and 3 months during the pilot pragmatic RCT will be added to the distribution of ED visit costs for each individual obtained under Objective 1. Once all costs have been added, an average will be calculated to obtain an average cost per participant at 3 months, for each model of care (Objective 2 & 3 –decision tree). The questionnaires provided data on resources used by each participant during follow-up such as ED re-visits for the same condition, number of consultations with other health professionals in the public and private sector, imaging tests used, etc. The costs of all resources used in the public healthcare system will be drawn from public cost repositories data from the *Régie de l’assurance-maladie du Québec* (RAMQ) (costs related to the emergency physician and other physicians consulted, drugs, laboratory analysis, imaging tests) [47]. Hourly rates for the primary contact physiotherapist and other health professionals consulted (e.g., massage therapist, chiropractor, osteopath) will be derived from a search of the grey literature and will be based on rates in effect within the private healthcare system, since the majority of these professionals work within this system [47]. Costs related to the use of technical aids (e.g., cane, crutches, walker) will also come from a grey literature search. It should be noted that the salary data available from human resources for all healthcare professionals (physicians and allied health professionals) considered will not allow for variability in hourly costs. The only source of variability considered for the purpose of these analyses will be that related to the time required for ED processes. Utility scores were obtained at the initial visit [48] and at 1 and 3 months using the EQ-5D-5L, a generic standardized questionnaire designed to measure health status in an economic and clinical evaluation [49]. The EQ-5D-5L has been found to be reliable, valid, and sensitive to change [50, 51]. The difference in utility scores between the 3-month follow-up and baseline will be calculated for each participant using area-under-the-curve analyses. Once the difference in utility scores will be calculated for each participant, the differences will be averaged to obtain the average gain or loss in utility scores per ED care model. The mean gain or loss in utility scores will then be transformed into QALYs. The efficiency values and the costs from 3 to 24 months required to run the Markov model (Objective 3) for the three models of care will be taken from the literature.

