
### Data analysis and interpretation of results

As part of Objective 1, a mapping of the care pathways encountered will be completed for each type of MSKD encountered in our study population (i.e., low back pain, neck pain, upper limb, lower limb) (Fig 1). The unit cost of each of the resources, consumables and indirect costs required in each process of care of the care pathway will be calculated and multiplied by the duration of each process to obtain the cost related to each process of care present in the care pathway. The costs associated with each process will be summed to obtain the total cost of the ED care pathway specific to each MSKD and each model of care (i.e., emergency physician or primary contact physiotherapist and emergency physician management). A generalized linear model with a Gamma distribution and log link will be used to test whether there is a significant difference in the costs of managing equivalent MSKDs between the two models of care [52, 53].

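### As written, follow-up ED re-visits are priced from RAMQ items and the index ED visit by TDABC, so one 3-month total values the same kind of event on two cost bases

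*Protocol article*

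**What the plan says.** **Index visit.** Under Study design and costing approaches, Objective 1 uses TDABC, which costs each care process as a rate per minute times the minutes taken. Study outcomes gives the source of the inputs: "The costs related to ED management (medical and non-medical staff, imaging, medication, consumables, maintenance, etc.) were obtained via a formal request" to the hospital's Finance Department. Data analysis and interpretation of results adds indirect costs: "The unit cost of each of the resources, consumables and indirect costs required in each process of care of the care pathway will be calculated".

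**Follow-up.** Study outcomes says the 1- and 3-month questionnaires record "resources used by each participant during follow-up such as ED re-visits for the same condition", among other items. The next sentence sets the price source: "The costs of all resources used in the public healthcare system will be drawn from public cost repositories data" from RAMQ, with a bracket listing "costs related to the emergency physician and other physicians consulted, drugs, laboratory analysis, imaging tests".

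**Summation.** The same section says each participant's follow-up costs "will be added to the distribution of ED visit costs for each individual obtained under Objective 1". The resulting mean 3-month cost feeds Objective 2 and the decision tree of Objective 3.

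**Expected effect.** The Introduction reports that "this model of care was associated with fewer repeat visits to the ED for a similar condition for up to one month" after the initial visit. It gives no rate. One of the sources cited there is also cited under Data collection as the report of the pilot RCT that supplies the data for this evaluation.

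**The concern.** An ED visit for a given MSKD is the same kind of event at day 0 and at week 3. If the first carries nursing, clerical, consumable, maintenance and overhead costs and the second does not, the 3-month total mixes two cost concepts. The mixture cancels between arms only if re-visit rates are equal, and the protocol itself reports that they are not, at least up to one month.

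At stake is the incremental cost in Objective 2 and in the 0–3 month decision tree. It is affected under both perspectives, because health system costs enter each. The cost of adding a physiotherapist would be charged in full at the index visit, while an avoided re-visit would be credited only at the listed items. The planned uncertainty analyses would not reveal this. The bootstrap carries the same re-visit price through every replicate. The three scenarios (extreme utilities for missing follow-up, exclusion of outliers, Markov states based on pain interference) do not vary the basis of that price.

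**Working it through.** The protocol states no unit cost, re-visit rate or ICER, so there is no figure to reproduce. The check is a comparison of texts followed by an algebraic bound.

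**1. Components named for each event**

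| Component | Index visit (TDABC) | Re-visit (RAMQ list) |
|---|---|---|
| Physician | yes | yes |
| Drugs | yes | yes |
| Imaging | yes | yes |
| Laboratory | not named separately | yes |
| Non-medical staff | yes | not listed |
| Consumables | yes | not listed |
| Maintenance | yes | not listed |
| Indirect costs | yes | not listed |

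**2. Effect on incremental cost.** Define:
- *C*: full cost of an ED visit.
- *m*: share of *C* that the listed RAMQ items do not cover.
- *d0*: index-visit cost difference, physiotherapist minus usual care.
- *dr*: re-visits per patient, usual care minus physiotherapist.

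With all other follow-up costs equal between arms:
- consistent pricing: ΔC = *d0* − *C*·*dr*
- pricing as written: ΔC = *d0* − (1 − *m*)·*C*·*dr*
- shift (as written minus consistent): *m*·*C*·*dr*

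The shift is positive, that is, against the physiotherapist model, when *m* > 0 and *dr* > 0. It is zero if *dr* = 0. It reverses if the RAMQ prices exceed their hospital counterparts by more than the omitted components, which makes *m* negative.

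**3. Illustration.** All inputs are assumptions: *C* = 100, *m* = 0.2 to 0.6, *dr* = 0.05 to 0.20. Entries are *m* × 100 × *dr*.

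| *m* | *dr* = 0.05 | *dr* = 0.10 | *dr* = 0.20 |
|---|---|---|---|
| 0.2 | 1 | 2 | 4 |
| 0.4 | 2 | 4 | 8 |
| 0.6 | 3 | 6 | 12 |

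The shift is therefore 1% to 12% of one ED visit cost per patient.

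**4. Can the sign change?** Take *d0* = +5, *m* = 0.6, *dr* = 0.10. Consistent pricing gives 5 − 100 × 0.10 = −5. Pricing as written gives 5 − 0.4 × 100 × 0.10 = +1. The gap is 6, as in the table. This example was chosen to show that a reversal is possible; it is not an estimate of what will occur.

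**The case against.** The strongest reply is that the sentence is being read too tightly. It does not say that it is confined to follow-up, and the same paragraph goes on to the physiotherapist's hourly rate and the duration of ED processes, which belong to the costing of the index visit. Data collection says public repositories serve all three objectives and introduces its examples as examples. The repositories may then supply unit prices to TDABC and not a separate tariff for a whole visit. The bracketed list may be illustrative, and a condensed article need not name a source for every cost item.

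Part of this stands. The list may not be complete, and no sentence says that nursing or overhead will be left out of a re-visit. A reader might infer that re-visits are certainly under-valued and the ICER certainly biased against the physiotherapist model. The documents do not support that: it depends on unit prices and re-visit rates they do not give, and the reported reduction covers one month, not three.

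What does not fall is the inconsistency. The sentence is a stated rule covering all public-system resources. It directly follows the one that names re-visits, and its bracket carries no marker of incompleteness. It also names the emergency physician, who in follow-up would most naturally be met at a re-visit. If the sentence is meant to cover the index visit too, it sits awkwardly with the Finance Department as the source of medical staff costs, and a re-visit still has no named source for its remaining ED cost.

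**Conclusion.** The point holds as an inconsistency in the costing rule, with a conditional consequence. Read naturally, the plan values the index visit and a re-visit on different bases and sums them. Two conditions turn this into a shift in incremental cost against the physiotherapist model: the listed RAMQ items must cover less than the full ED cost, and re-visits must be fewer in that arm. The protocol supports the second up to one month, without a rate; the first is plausible but unverified.

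The size is *m* × *C* × *dr*. The documents supply none of the three terms, so the 1% to 12% range rests wholly on assumptions and the true effect may be small. It reaches Objective 2 and the 0–3 month decision-tree costs of the two models observed in the RCT. Objective 1 is unaffected. The 3–24 month Markov costs and all parameters of the physiotherapist-alone model come from the literature and lie outside the point.

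**What to change.** 1. For the two RCT-observed models, state that each ED re-visit is valued at the Objective 1 TDABC cost of the usual-care pathway for the same MSKD type, carrying its time distribution. Keep RAMQ and other repository prices for resources used outside the ED.
2. Prevent double counting. Do not add RAMQ physician, drug or imaging items for a re-visit on top of the TDABC cost. Where imaging or drug items in the questionnaire cannot be separated from a re-visit, use the TDABC cost net of imaging and drugs.
3. Add a sensitivity analysis on the re-visit unit cost, running from the listed RAMQ items alone to the full TDABC cost.

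If the list was meant as illustrative, the minimum is to say so and to name the source for the rest of a re-visit's ED cost.

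**Cost.** A few sentences in the costing plan and one extra analysis; Objective 1 already produces the pathway costs. Some work may be needed to establish which questionnaire items belong to a re-visit. The drawback is the assumption that a re-visit resembles an index usual-care visit at this hospital, which the protocol does not establish; the sensitivity analysis is there to show how much depends on it.

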### Data collection

Objectives 1, 2 and 3 will be achieved in part using data collected through a two-arm pilot pragmatic randomized clinical trial (RCT) conducted in the ED of the CHUL, one of the five sites of the CHU de Québec—Université Laval (UL) (Quebec City, Canada) from September 2018 to March 2019 (n = 78). This trial aimed to compare the effects of management by a primary contact physiotherapist to usual care provided by an emergency physician for persons presenting with a minor MSKD on their clinical course (pain and pain interference) and the use of resources at ED discharge and after 1 and 3 months post-visit [29]. Two groups of participants were compared: one group managed by a primary contact physiotherapist and an emergency physician and one group managed by an emergency physician alone.

Data were collected at the initial ED visit and at the one- and three-month post-visit follow-ups. While more details of the data collection procedures can be found in our previous paper [29], any person presenting to the ED who met the inclusion and exclusion criteria was seen by a member of the research team who confirmed eligibility, obtained informed consent, and ensured completion of baseline questionnaires. The participant was then randomized to either study group: primary contact physiotherapist + emergency physician management or usual management by the emergency physician alone. After the ED visit was completed, participants were contacted at 1 and 3 months either by phone or email to complete post-visit follow-ups. The supplementary data needed to meet the three Objectives will come from some of the CHU de Québec—UL administrative databases (nominative data: SIURGE (ED management software), Cristal-Net (patient electronic record), and the CHUL’s ED pharmacy transactions directory; administrative data: prescription and over-the-counter drug costs repository), the scientific literature, and public cost repositories (e.g., salaries of general practitioners and specialists, see https://www.msss.gouv.qc.ca/inc/documents/ministere/acces_info/seance-publique/etude-credits-2018-2019/Reponses-aux-questions-generales-et-particulieres-RAMQ.pdf; laboratory analysis costs, see https://publications.msss.gouv.qc.ca/msss/fichiers/2017/17-922-05W.pdf).

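### The ED physiotherapist, who works only in the intervention arm, is assigned a private-sector hourly rate that conflicts with the hospital and public cost sources stated for other ED staff

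*Protocol article*

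**What the plan says.** All references are to the protocol article, Materials and methods.

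- **Study outcomes, first paragraph (Objective 1).** "The costs related to ED management (medical and non-medical staff, imaging, medication, consumables, maintenance, etc.) were obtained via a formal request" to the hospital's Finance Department. Process times come from staff estimates checked by observation.
- **Study outcomes, second paragraph (Objectives 2 and 3).** Follow-up costs are added to each participant's ED visit cost from Objective 1. "The costs of all resources used in the public healthcare system will be drawn from public cost repositories data" of the provincial insurer, and the emergency physician is listed among those resources. Next, "Hourly rates for the primary contact physiotherapist and other health professionals consulted" are to come from a grey-literature search and "will be based on rates in effect within the private healthcare system, since the majority of these professionals work within this system". The examples given are massage therapists, chiropractors and osteopaths.
- **Same paragraph, a little later.** According to the article, "the salary data available from human resources for all healthcare professionals (physicians and allied health professionals) considered will not allow for variability in hourly costs". ED process time is the only quantity allowed to vary.
- **Data collection.** The trial was "conducted in the ED of the CHUL, one of the five sites of the CHU de Québec", with "one group managed by a primary contact physiotherapist and an emergency physician and one group managed by an emergency physician alone". The physiotherapist-alone model was not observed in the trial, and all its parameters, costs included, come from a literature review.
- **Data analysis and interpretation of results.** Objective 1 builds each pathway cost from unit costs, including indirect costs, multiplied by duration. Objectives 2 and 3 are run from Health system and Societal perspectives.

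**The concern.** The ED physiotherapist is the resource that defines the comparison. As written, that clinician gets a private-market rate, while the emergency physician gets a public or hospital cost. A private rate is a market price. It is not evidently what the health system bears when the hospital supplies the physiotherapist, and the Health system perspective is one of the two planned analyses.

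The emergency physician is in both arms, so an error in the physician's rate cancels to the extent that physician time is similar. The ED physiotherapist's time is charged in one arm, so an error in that rate passes in full into the cost difference. The three-month ICER has that difference as its numerator. Its denominator is likely to be small over so short a horizon, so a modest cost shift can become a large shift per QALY.

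**Working it through.** **1. Which role does the private-rate sentence name?** The objectives, Data collection and Data analysis sections all use primary contact physiotherapist for the ED clinician in the intervention model. The Introduction also uses the term for primary-care settings, but the Methods do not. The sentence therefore names the trial's ED role.

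**2. Does the stated reason fit that role?** The reason is that most of these professionals work privately. That fits the three community examples. It does not fit a physiotherapist seeing patients in a hospital ED.

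**3. Sources side by side.**

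| Resource | Source stated |
|---|---|
| ED medical and non-medical staff (Objective 1) | Hospital Finance Department |
| Physicians and allied health professionals, hourly cost | Human-resources salary data, no variability |
| Emergency physician and other public resources | Public repositories |
| Primary contact physiotherapist | Grey literature, private-system rates |

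The first two rows are compatible, since both come from the hospital side. The conflict is between the last row and the rest.

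**4. Effect if the private rate is used at the ED visit.** The article gives no rate, no physiotherapist time and no incremental cost, so there is no figure to reproduce. Physiotherapist time is charged in one arm, so

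shift in incremental cost per patient = (private rate − hospital cost per hour) × minutes / 60

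shift in ICER = that shift / incremental QALY

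**5. Illustration, all inputs assumed.** Hospital loaded cost CAD 40–60/h, private rate CAD 60–120/h, 15–60 minutes. Shift in CAD per patient:

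| Hospital | Private | 15 min | 30 min | 45 min | 60 min |
|---|---|---|---|---|---|
| 40 | 60 | 5 | 10 | 15 | 20 |
| 40 | 90 | 12.5 | 25 | 37.5 | 50 |
| 40 | 120 | 20 | 40 | 60 | 80 |
| 60 | 60 | 0 | 0 | 0 | 0 |
| 60 | 90 | 7.5 | 15 | 22.5 | 30 |
| 60 | 120 | 15 | 30 | 45 | 60 |

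If the private rate were 20% below the loaded hospital cost, 30 minutes would give (0.8 − 1) × 30 = −6 hospital-rate minutes, so the sign can reverse.

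For an assumed incremental QALY of 0.005 to 0.02, shifts of CAD 5 to 40 move the ICER by 5/0.02 = 250 up to 40/0.005 = 8,000 per QALY. The largest cell in the table gives 80/0.005 = 16,000.

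**6. Would the planned uncertainty analyses show it?** Hourly rates are held fixed, so the bootstrap and the Monte Carlo simulation carry the chosen rate as a constant. The three scenarios concern extreme utility values for missing participants, exclusion of outliers, and redefinition of the Markov states. None varies the rate.

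**7. Where it would enter.** It would enter the three-month ICER and the decision tree for the combined model, because ED visit costs feed both. It would enter Objective 1 only if the private rate is also used in the pathway costing there.

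**The case against.** The strongest reply is that the sentence was meant for follow-up only. It sits in a list of resources reported in the follow-up questionnaires, uses the word *consulted*, and gives only community examples. The sentence before it treats the emergency physician in the same way, although ED medical staff had already been costed through the Finance Department. On that reading the index visit is costed entirely from hospital data, and private rates touch only follow-up visits, which occur in both arms.

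This reading is plausible, and it means one cannot say that the ED visit will be priced privately. It does not remove the conflict, because the sentence names the ED role and nothing limits it to follow-up. It also leaves a gap: the questionnaires record consultations in both sectors, yet non-physician professionals are given only a private rate. The rule for public resources might cover their public visits, but its list does not mention them.

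A reader might infer several stronger things that the article does not support:

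- **Objective 1 is certainly affected.** The Objective 1 text points to Finance Department costs and mentions no private rate.
- **The error counts against the physiotherapist model.** That needs a private rate above the loaded hospital cost, and neither figure is given.
- **Overhead is counted twice.** This happens only if the private rate includes overhead and the TDABC indirect costs are added on top.
- **Every physiotherapist model in Objective 3 is affected in the same way.** The physiotherapist-alone model takes its costs from the literature, as do the 3–24 month costs of all three models.

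**Conclusion.** The concern stands as a stated conflict over a key cost input. Taken literally, the private-rate sentence puts the clinician who distinguishes the arms on a different cost basis from the other ED staff, for a reason that does not fit that clinician. If it is applied to the ED visit, the incremental cost shifts by the rate difference times physiotherapist time, in one arm only, and no described uncertainty analysis would reveal it.

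It is not an established bias. Whether it occurs depends on which paragraph governs the index visit, and its size and sign depend on rates and minutes that the article does not give. The figures of CAD 0 to 80 per patient and CAD 250 to 8,000 per QALY (16,000 at the extreme) only illustrate how sensitive the result could be under assumed inputs. The text should be settled before the analysis.

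**What to change.** 1. Cost the ED physiotherapist at the index visit from the hospital Finance and human-resources data, on the same basis as the emergency physician. Let overhead enter once, through the TDABC indirect costs. State that this cost carries into Objective 2 and into the decision tree for the combined model.
2. Restrict private rates to follow-up visits actually made in the private sector, and use public unit costs for public visits.
3. Add a one-way sensitivity analysis on the ED physiotherapist's hourly rate, with the private rate as one of its values.
4. For the physiotherapist-alone model, take resource use from the literature as planned, but value the physiotherapist's time at the same hospital unit cost where the source reports time or resource use separately.

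The cost is small: a few sentences of text and one additional sensitivity run. The article says the ED staff costs were already obtained. It does not list the physiotherapist by name among them, so coverage should be confirmed. Item 4 adds some data extraction and will not be possible for every source.
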